### **3) Final assessment and consent for participation**

At this meeting, each potential participant will meet the Chief Investigator of this study and a research nurse based at the CRF of RIE. The researcher will discuss with the potential participant any questions they may have about the study. The CRF nurse will help to check if this potential participant has adequate capacity in cognition and communication. This may identify a few people who are not eligible for the trial. For those patients, the researcher will explain why this trial is not suitable for them. Potential participants who are eligible for this trial and willing to take part will be asked to sign a consent form for taking part in the trial. This consent form will also be signed by the researcher and the CRF nurse.

After signing the consent, the participant will be asked to complete four of questionnaires for baseline assessment for the following clinical outcomes:

- Fatigue: Fatigue Assessment Scale (FAS) and a case definition for post-stroke fatigue
- Independence in daily life: Nottingham Extended Activities of Daily Living (NADL)
- Stroke-specific health-related quality of life: Stroke Impact Scale (SIS)

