### *For clinical outcomes*

6. To test the feasibility of completing questionnaires for clinical outcomes

The secondary objective is to perform a before-and-after analysis of clinical outcomes.

- 1) Fatigue, measured by the Fatigue Assessment Scale (FAS) and by a Case Definition of post-stroke fatigue
- 2) Depression, measured by Patient Health Questionnaire-9 (PHQ-9)
- 3) Independence in daily life, measured by Nottingham Extended Activities of Daily Life (NADL)
- 4) Stroke-specific health-related quality of life, measured by Stroke Impact Scale (SIS)

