#### **Exclusion criteria**

1) Severe depression

Depression will be assessed by the Patient Health Questionnaire-9 (PHQ-9), of which a total score of 15 or more would indicate severe depression. We will exclude patients with a total score of PHQ-9 of 15 or more. This is because there is a large overlap between symptoms of fatigue and depression. Fatigue accompanying post-stroke depression is often relieved when the depression is adequately treated.

2) Significant impairments that preclude them from being benefit from the intervention, for example:

- Severe cognitive deficits (This would preclude them from fully understanding the intervention materials)
  - Severe aphasia (Participants need to be able to carry out effective conversation with the therapist)
  - Other significant difficulties in verbal communication
- 3) Medically unstable in the opinion of a medical clinician (This will be determined by contacting their General Practitioners)
  - 4) Have another unfavourable condition that could impact results (e.g. substance abuse)
  - 5) Currently in the nursing home
  - 6) Currently in other research studies that might affect fatigue or add significant burden to the participant, for example, studies have outcome measures for fatigue or involve physical training (e.g. the FOCUS study)

Multiple stages will be taken to determine the eligibility for participation, including:

- Screening the discharge summary stored in the TRAK system, which is the electronic database of the NHS (e.g. for age, time after stroke, settlement in Lothian)
- Contacting the General Practitioners (GP) of the potential participants (e.g. for current depression, communication capacity, medical stability, unfavourable condition, whether in other research studies)
- Reviewing the results of survey questionnaire completed by the potential participants (e.g. for post-stroke fatigue and depression)
- Telephone conversation and face-to-face meeting between the potential participants and the researchers (e.g. for capacity of cognition and communication)

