#### **2) Further assessment of eligibility by a survey for post-stroke fatigue and depression**

For potential participants who meet all of the above inclusion criteria and do not have any of the exclusion criteria, they will receive an invitation pack which provides the information of a survey for post-stroke fatigue and invites them to complete the survey.

The invitation pack will contain the following items:

- 1) An invitation letter to the survey (signed by the responsible doctor of the stroke survivor in the Stroke Ward)
- 2) An information sheet about the survey
- 3) A consent form
- 4) A questionnaire for post-stroke fatigue and depression

Potential participants who are willing to take part in this survey will be asked to sign the consent and complete the questionnaire, and return them to the research team using a stamped addressed envelope.

By signing the consent form, the participants will:

- Give consent to take part in the survey (to complete the questionnaire)
- Give permission to the research team to access their medical records
- Give permission to receive further contact from the research team
- Allow their GPs to be informed of their participation and their results of survey

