- For participants who have post-stroke fatigue and have a total score of PHQ-9 of 15 or more, we will not invite them to the trial and will suggest them see their GPs to provide health care for depression.

- For participants who do not have post-stroke fatigue, we will not invite them to the trial. If they have a total score of PHQ-9 of 10 or more, we will suggest them see their GPs to provide health care for depression.

One week after sending out the invitation letter and information sheet of the trial to potential participants, a researcher will contact them by telephone 1) to answer any questions that they may have, and 2) to ask if they would like to take part in the trial.

For patients who are interested in taking part in the trial or would like to learn more about this study, the researcher will invite them to a face-to-face meeting at the Clinical Research Facility (CRF) of the Royal Infirmary of Edinburgh (RIE).

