### **Step 3: Post-treatment assessment**

At the end of the last face-to-face session, each participant will take home five questionnaires for post-treatment assessment, including:

- Fatigue Assessment Scale (FAS)
- A case definition of post-stroke fatigue
- Patient Health Questionnaire-9 (PHQ-9)
- Nottingham Instrumental Activity of Daily Life (NADL)
- Stroke Impact Scale (SIS)

The participant will be asked to complete these questionnaires at home and return to the research team within a week. If the questionnaires have not been returned within two weeks, the researcher will contact the participant by telephone to remind them and, if necessary, complete the questionnaires with the participant through the telephone.

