## Clinical outcomes

Clinical outcomes will be assessed before treatment, immediately after treatment, one-month and three-month after treatment, respectively, including the following measures:

- Fatigue: **Fatigue Assessment Scale** and a **case definition for post-stroke fatigue**
- Depression: **Patient Health Questionnaire-9**
- Independence in daily life: **Nottingham Extended Activities in Daily Living**
- Stroke-specific health-related quality of life: **Stroke Impact Scale**

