## Data analysis

Descriptive statistics will be used to analyse the results. An interim analysis will be performed at one-month after the last face-to-face session. The final analysis will be performed at the end of the trial when all data collection, entry and validation are completed (three-month after the last face-to-face session). The data of feasibility will be analysed of a group of 12 participants. The clinical data will be analysed both individually and by group.

The number of participants attending, missing, and withdrawal (from therapy sessions and/or follow up) will be recorded and the relevant rates will be calculated. The success of

recruitment strategies will be measured by summarising responding, eligibility, and consent rated. The feasibility of assessment for clinical outcomes will be determined by the level of missing data of individual items and for the entire outcome questionnaires.

To investigate changes in clinical outcomes, we will report mean change in scores of each questionnaire with 95% confidence interval (CI) from pre-treatment assessment to post-treatment assessment. In addition, the change of scores for each clinical outcome from post-treatment to one-month follow up, and from post-treatment to three-month follow up, will be analysed to determine whether any benefits (if applicable) acquired during the therapy sessions could be maintained one month and three months after the last face-to-face session, respectively.

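### PHQ-9 is missing from the baseline pack, so the depression change appears to start from an earlier postal score cut off at 15, which slightly understates improvement

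*Protocol*

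**What the plan says.** Under *3) Final assessment and consent for participation*, after consent "the participant will be asked to complete four of questionnaires for baseline assessment". The list that follows has exactly four instruments (FAS, case definition, NADL, SIS), so the count and the list agree and PHQ-9 is absent from both.

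Under *Step 3: Post-treatment assessment*, "each participant will take home five questionnaires for post-treatment assessment". These are the same four plus PHQ-9. Steps 4 and 8 reuse that set at one and three months.

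Depression by PHQ-9 is listed under the secondary objective, a before-and-after analysis. *Clinical outcomes*, whose list includes PHQ-9, says: "Clinical outcomes will be assessed before treatment, immediately after treatment, one-month and three-month after treatment". *Data analysis* promises a mean change with 95% CI for each questionnaire "from pre-treatment assessment to post-treatment assessment".

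Before treatment, PHQ-9 appears only in the recruitment survey, whose invitation pack contains "A questionnaire for post-stroke fatigue and depression". The same score decides entry. *Exclusion criteria* states: "We will exclude patients with a total score of PHQ-9 of 15 or more", and Table 2 applies that cut-off to the survey result.

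**The concern.** If the survey score is the starting value, the PHQ-9 change differs from the other changes in two ways.

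- **Timing.** The survey comes before the result letters to participant and GP, the trial invitation, the telephone call and the visit at which the other outcomes are measured. The study has no control arm, so change over that extra interval cannot be separated from change over the treatment period.
- **Selection.** Respondents scoring 15 or more are removed on the very variable being compared. Those who stay in have, on average, scores that are low partly by chance, and these tend to rise on retest.

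Two further uses are touched. Step 5 compares each participant's baseline with later scores, and Step 6 treats telling participants the result as part of the intervention. Item 4 of *Feasibility outcomes* counts missing items for the baseline assessment, so PHQ-9 completion at that visit would go unassessed.

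**Working it through.** **Sample size.** The recruitment figure reproduces: 100 × 0.50 × 0.30 × 0.80 = 12. The Protocol states no other derived figure that bears on this point.

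**Instruments by assessment.**

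| Assessment | Forms | PHQ-9 included |
|---|---|---|
| Postal survey | fatigue question and PHQ-9 | yes, used for entry |
| Consent visit (baseline) | 4 | no |
| Post-treatment | 5 | yes |
| One month, three months | same 5 | yes |

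**Gap.** The telephone call is made "One week after sending out the invitation letter and information sheet of the trial to potential participants". That invitation follows the returned survey, and the visit follows the call. The survey therefore precedes the visit by more than a week. No maximum is given; the three-month recruitment window in the *Timeline* is not stated as a limit on this interval.

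**Size of the selection effect.** The Protocol gives no PHQ-9 mean, SD or reliability. The assumptions are a mean of 6 to 12, SD of 4 to 6 and retest correlation r of 0.7 to 0.9 among fatigued respondents, with no real change. Scores are whole numbers and 15 or more is excluded, so the boundary is 14.5:

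a = (14.5 − mean)/SD

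expected drift = (1 − r) × SD × φ(a)/Φ(a)

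Middle case, mean 8, SD 5, r 0.8: a = 6.5/5 = 1.30; φ/Φ = 0.190; drift = 0.2 × 5 × 0.190 = +0.19.

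The 95% CI half-width at n=12 is 2.201 × SD of change/√12. The SD of change comes from a simulation with whole-number scores held to 0–27, which also agreed with the drift formula. In the middle case it is about 3.01, giving 2.201 × 3.01/3.464 = 1.91. The last column is the simulated share of those admitted who would score 15 or more on retest, times 12.

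| Mean | SD | r | a | φ/Φ | Drift | CI half-width | 15 or more on retest, of 12 |
|---|---|---|---|---|---|---|---|
| 6 | 4 | 0.9 | 2.125 | 0.042 | +0.02 | 1.11 | 0.007 × 12 = 0.1 |
| 8 | 5 | 0.8 | 1.30 | 0.190 | +0.19 | 1.91 | 0.047 × 12 = 0.6 |
| 10 | 5 | 0.8 | 0.90 | 0.326 | +0.33 | 1.94 | 0.082 × 12 = 1.0 |
| 12 | 6 | 0.7 | 0.417 | 0.553 | +1.00 | 2.76 | 0.176 × 12 = 2.1 |

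The first and last rows are the extremes of the grid. Higher PHQ-9 means more depression, so a positive drift looks like worsening. Even in the last row it is 1.00/2.76 = 0.36 of the half-width.

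**The case against.** The best defence is that nothing is contradicted. The survey is completed before treatment, so the statement in *Clinical outcomes* can be met with it, and a baseline list of exactly four forms may reflect a choice not to repeat a form already filled in. The survey is also completed at home, as the later forms are. The other outcomes are not measured at the start of therapy either, since the first session is on a later date. GP contact about current depression may thin the upper tail and make the drift smaller still.

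Much of this stands. The Protocol can be carried out with the survey score, and the timing difference is one of degree. But no section names or dates that score as the baseline, so using it is an inference, and the selection effect remains under that reading.

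A reader might infer more than the document supports:

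- **That the depression result would be made to look better.** The drift runs the other way.
- **That the survey score is invalid as a baseline.** The expected drift is small against the precision of 12 people, and every input to it is assumed.
- **That missing PHQ-9 items cannot be counted.** They can be counted on the returned survey form; only completion at the baseline visit goes unassessed.

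**Conclusion.** The concern holds in a limited form. The baseline pack omits an instrument that the Protocol treats as a before-and-after outcome. The only earlier PHQ-9 has a different, undated starting point and is truncated by the entry rule. Under the stated assumptions, the truncation alone moves the mean pre-to-post change by about +0.02 to +1.0 points, against a likely CI half-width of about 1.1 to 2.8 points. The effect of the extra interval cannot be quantified from the document. The planned changes from post-treatment to one and three months do not use the baseline and are unaffected.

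Severity is low to moderate. Depression change is one secondary outcome of an uncontrolled 12-person feasibility study, and effectiveness is left to a later trial. It is still worth settling before recruitment, because a baseline not collected before the first session cannot be recovered.

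**What to change.** Add PHQ-9 to the baseline list in *3) Final assessment and consent for participation*, making five forms as at the later assessments. In *Data analysis*, name that value as the pre-treatment PHQ-9, and keep the survey score for screening. This aligns the starting point with the other outcomes and brings PHQ-9 into the baseline missing-item count. It removes the selection drift to the extent that errors on the two occasions are independent.

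The cost is a few minutes per participant at an existing visit, plus one consequence to settle. Some participants who have already consented may score 15 or more at baseline (about 0.1 to 2.1 of 12 under the assumptions above). The sponsor must reconcile *Exclusion criteria* with the consent-visit section on how such a score relates to eligibility.

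If the form is not added, the Protocol should at least name the survey score as the baseline, record its date and report the selection effect. That removes the ambiguity but leaves the gap and the drift.

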#### **Clarification of the questionnaires**

If any item of questionnaires is unanswered or appears inconsistent with the other answers, or if the participants give inappropriate answers to the questions of the case definition, the researcher will clarify the reasons with the participant.

Finally, the participant will be asked to choose a date from a list of dates for the first therapy session (the list is provided by the therapist before this meeting).

For each participant, the researcher will send a letter to inform their GPs that they are taking part in this trial for post-stroke fatigue.

## **Step 2: Six therapy sessions**

Participants will be invited to the Department of Psychology at the Astley Ainslie Hospital or the Clinical Research Facility at the Royal Infirmary of Edinburgh for therapy sessions. The intervention consists of six face-to-face sessions. A clinical psychologist, who is the therapist of this intervention, will provide support for the participant throughout the trial. During these sessions, the participant will discuss their fatigue-related problems with the therapist and work on a treatment manual to learn skills to overcome their fatigue. Each session will last about one hour and the first session will have an extra 30 minutes at the beginning to engage the participant in a collaborative therapeutic relationship with the therapist. There will be an interval of two weeks between sessions. During the intervals, the participant will be required to do some tasks at home, including keeping a diary, carrying out an activity plan, or reading sections of the treatment manual.

The intervention incorporates both psychological and rehabilitative approaches to challenge participants' cognition and behaviours in response to fatigue. With support from the therapist, the participant will explore their own problems in thoughts (their beliefs about fatigue and their ability to overcome it), emotions (their emotional responses to fatigue-related problems), and behaviours (physical activities in daily life) which may potentially contribute to their fatigue. Then they will work together to find out individualised treatment strategies to help the participant reduce the impact of fatigue on their daily life. The therapeutic components of the intervention, as well as the aim, rationale and expected outcomes for each component are summarised in Table 3.

**Table 3 A summary of the intervention**

| Therapeutic components                      | Aim                                                                        | Rationale                                                                                                                                                                                                                                                                                   | Expected outcomes                                                                                                                                                                                                                 |
|---------------------------------------------|----------------------------------------------------------------------------|---------------------------------------------------------------------------------------------------------------------------------------------------------------------------------------------------------------------------------------------------------------------------------------------|-----------------------------------------------------------------------------------------------------------------------------------------------------------------------------------------------------------------------------------|
| Education about post-stroke fatigue         | To provide individualised treatment rationale                              | 
Post-stroke fatigue is a complex symptom that affects physical, emotional, cognitive and behavioural functions;
 
The impact of fatigue on life is temporary and reversible;
 
Building up confidence to overcome fatigue is very important for this psychological therapy
 | 
Participants will understand their own problems that contribute to fatigue;
 
Participants will regain self-confidence in overcoming fatigue;
 
Participants will be willing to engage in this treatment therapy
 |
| Regulating the sleep pattern                | To develop a regular pattern of sleep                                      | 
It is common for stroke survivors to have problems of sleep;
 
Disturbed sleep is a common cause for the feeling of tiredness
                                                                                                                                                   | Participants will develop a regular pattern of sleep with adequate amount of time for sleep each night, a fixed getting up time, and avoiding naps during the day                                                                 |
| Graded activity programme                   | To gradually increase physical capacity                                    | 
Adaptation of activity patterns to current energy level;
 
Balancing daily activities, rest and sleep;
 
Gradually increasing the amount of physical activity doing each day
                                                                                               | Participants will develop a more active pattern of daily life, with different activities spread over the week and balanced with planned rests during the day                                                                      |
| Challenging unhelpful thoughts and emotions | To identify and deal with any emotions or thoughts that block the progress | Thoughts, emotions and behaviours are interacted with each other and are contributing to fatigue symptoms                                                                                                                                                                                   | Participants will be aware of unhelpful thoughts and emotions and will be able to act in a more positive and effective pattern                                                                                                    |
| Managing blocks and setbacks                | To identify and deal with (potential) difficulties in making progress      | It is understandable that people will have difficulties in changing the way they used to think and act                                                                                                                                                                                      | Participants will be prepared for potential problems and will be able to manage, should they occur                                                                                                                                |

### **Step 3: Post-treatment assessment**

At the end of the last face-to-face session, each participant will take home five questionnaires for post-treatment assessment, including:

- Fatigue Assessment Scale (FAS)
- A case definition of post-stroke fatigue
- Patient Health Questionnaire-9 (PHQ-9)
- Nottingham Instrumental Activity of Daily Life (NADL)
- Stroke Impact Scale (SIS)

The participant will be asked to complete these questionnaires at home and return to the research team within a week. If the questionnaires have not been returned within two weeks, the researcher will contact the participant by telephone to remind them and, if necessary, complete the questionnaires with the participant through the telephone.

